**Specific methods**

**Developmental milestones**

Developmental milestones are assessed with parent-reported Ages and Stages Questionnaire (ASQ) 3rd edition. ASQ is a reliable and valid tool with high sensitivity and specificity for screening children requiring further developmental assessment. It comprises 21 age-specific questionnaires, covering 1 through 66 months of age, each with six items in each of five developmental domains: communication, gross motor, fine motor, problem solving, and personal/social (solitary social play and play with toys and other children) skills. Subscale scores range from 0 to 60. We chose the 12-month (11-13 months) and 24-month (23-25.5 months) questionnaires.

**Social-emotional problems and competencies**

Social-emotional problems and competencies are assessed with parent-reported Infant-Toddler Social Emotional Assessment (ITSEA). It is an adult-report questionnaire for 12-to 36-month olds. It includes 169 items containing a statement about the child's behavior during the last month. The scale has good psychometric properties.

## STATISTICAL ANALYSIS PLAN

### Sample size calculation and statistical analyses

We aim at detecting a 0.2 SD unit difference between continuous variables (developmental milestones and social-behavioral problems and competencies) and Odds Ratios >2.0 in categorical variables (mild developmental delay, clinically possible significant problems). In order to reach statistical power of 80% with significance level of 0.05, a total of 199 and 572 participants, respectively, are necessary. The trial was designed with a planned sample of 1000 study participants. We estimate a possible drop-out rate of 20% for each follow-up.

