**Primary outcomes**

Primary outcomes of the study are developmental milestones measured with the Ages and Stages Questionnaire (ASQ) at age 12 and 24 months and social-emotional problems and competencies measured with Infant-Toddler Social Emotional Assessment (ITSEA) at age 24 months.

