### Statistical methods

Standard statistical methods such as linear, logistic and Tobit and moderation analytic strategies with R/SPSS/MPlus will be used to study the impact of vitamin D supplementation and/or 25(OH)D concentrations, and relevant covariates, on main outcomes.

If needed, logarithmic transformation for nonnormal variables is performed in order to achieve normal distribution. Main outcome measures are analysed according to intention-to-treat and protocol-based manner.

To account for multiple testing and control for the false detection rate (FDR), *p*-values from the analysis within primary/secondary analysis were used to derive an FDR-adjusted *p*-values with FDR-procedure setting the false discovery rate at 0.05.

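### The neurodevelopment power statement uses an unadjusted 0.05, but the primary outcomes are judged on FDR-adjusted p-values from a family that is not listed, so the stated 80% does not apply to the plan's own success rule

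*Combined protocol and SAP*

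**What the plan says.** All references are to the neurodevelopment amendment unless stated.

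- **SAP, Sample size calculation and statistical analyses.** The targets are given as "We aim at detecting a 0.2 SD unit difference between continuous variables" and "Odds Ratios >2.0 in categorical variables". The power statement reads "In order to reach statistical power of 80% with significance level of 0.05, a total of 199 and 572 participants, respectively, are necessary". Multiplicity is not mentioned. The planned sample is 1000, with 20% drop-out expected at each follow-up.
- **SAP, Statistical methods.** To allow for multiple testing, p-values from the primary and secondary analyses "were used to derive an FDR-adjusted *p*-values with FDR-procedure setting the false discovery rate at 0.05". The reference given is the Benjamini-Hochberg paper. The p-values that form the primary family are not listed.
- **Protocol, Primary outcomes.** "Primary outcomes of the study are developmental milestones measured with the Ages and Stages Questionnaire (ASQ) at age 12 and 24 months", together with ITSEA problems and competencies at 24 months.
- **Protocol, Developmental milestones.** The ASQ questionnaires are described as "each with six items in each of five developmental domains", with subscale scores from 0 to 60. No ASQ total score is described.

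**The concern.** The power statement and the analysis rule use different criteria for a positive finding. The sample size section counts a test as positive at p < 0.05. Under BH over m tests, an outcome that is the only one affected must in effect reach about 0.05/m. No section links the two, so a reader would attach the 80% to the FDR-adjusted results.

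What is at stake is how a null result is read. A non-significant adjusted result would be set against 0.2 SD and an odds ratio of 2.0 as effects the study was powered to find. An effect confined to one ASQ domain is a natural possibility when five domains are scored separately, and that is where the adjustment costs most power.

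**Working it through.** **Inputs.** From the amendment's SAP: 0.2 SD, odds ratio 2.0, 80% power, level 0.05, totals of 199 and 572, 1000 planned, 20% drop-out per follow-up. From the main SAP: equal arms of 500. Analysed N is 1000 × 0.8 = 800 (400 per arm), or 1000 × 0.8 × 0.8 = 640 (320 per arm) if drop-out compounds over two follow-ups. Assumptions: two-sided tests (sidedness is not stated), normal approximation, and for the odds ratio a comparator-arm prevalence that the documents do not give.

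**1. The plan's own figures.**
- *199.* n per arm = 2(1.960 + 0.842)²/0.2² = 392.4, so 393 per arm and 786 in total. The printed 199 does not reproduce as a two-arm total. At 99.5 per arm, power at 0.05 is only about 29%. The number 199 does match a one-sample or paired t-test at 0.2 SD.
- *572.* With OR 2.0, p1 = 2p0/(1 + p0). At p0 = 9.9%, p1 = 18.0%, and 286 per arm gives 80% at 0.05. So 572 is reproducible, but only at a prevalence near 10%, which is not printed.

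**2. Size of the family.** Not stated. If every ASQ domain at each age and one ITSEA problem and one competence score are tested, 5 × 2 + 2 = 12. Dichotomised outcomes, ITSEA subscales or protocol-based repeats would raise this; instrument-level scores would lower it.

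**3. A design with exactly 80% per-test power, 12 tests.** The mean of the test statistic is 1.960 + 0.842 = 2.802. The first BH threshold is 0.05/12 = 0.00417, critical value 2.865. Power is Φ(2.802 − 2.865) = 47.5%. Simulating BH itself, with outcome correlations of 0, 0.3 and 0.5, gives per-outcome power of:

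| Outcomes truly affected, of 12 | Power under BH |
|---|---|
| 1 | about 48% |
| 2 | about 53% |
| 6 | 65-67% |
| 12 | 74-77% |

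**4. A lone 0.2 SD effect at the expected N.** Power is Φ(0.2√(n/2) − z), with z the two-sided critical value at 0.05/m. With n = 400 per arm, 0.2√200 = 2.828. The smallest effect detectable with 80% power is (z + 0.842)√(2/n).

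| Tests m | z | Power, 800 analysed | Detectable with 80% power, 800 analysed |
|---|---|---|---|
| 1 (unadjusted) | 1.960 | 81% | 0.20 SD |
| 3 | 2.394 | 67% | 0.23 SD |
| 5 | 2.576 | 60% | 0.24 SD |
| 10 | 2.807 | 51% | 0.26 SD |
| 12 | 2.865 | 48% | 0.26 SD |
| 24 | 3.078 | 40% | 0.28 SD |

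With 640 analysed and 12 tests, power is 37% and the detectable effect 0.29 SD.

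**5. Odds ratio 2.0, 12 tests, lone effect, 800 analysed.** Power is Φ{[(p1 − p0)√n − z√(2p̄(1 − p̄))] / √(p0(1 − p0) + p1(1 − p1))}, where p̄ is the mean of p0 and p1. At p0 = 9.9%: (0.0812 × 20 − 2.865 × 0.490)/0.487 = 0.45, so 67%.

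| Assumed prevalence | Power at OR 2.0 | OR detectable with 80% power |
|---|---|---|
| 5% | 34% | 2.7 |
| about 10% | 67% | 2.15 |
| 15% | 85% | 1.9 |
| 20% | 92% | 1.8 |

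**The case against.** The case against a strong claim has real weight.

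- **A reader might infer that the family has at least 12 tests.** The documents do not say so. The primary outcomes are named by instrument and age, and five domains are described without a statement that each is a separate primary test. Read as three instrument-by-age outcomes, a lone 0.2 SD effect keeps 67% power with 800 analysed. Twelve is an illustration, not a lower bound.
- **A reader might infer that the study simply has 48% power.** That is the least favourable pattern of effects. BH is not Bonferroni: its threshold loosens as more outcomes are affected, and the plan does not say that a single affected outcome is its planning case.
- **A reader might infer that an odds ratio of 2.0 would also be missed half the time.** The 572 is a stated requirement, not the expected N. With 800 analysed the answer depends on prevalence, and at 15-20% power exceeds 80% even with 12 tests.
- **A reader might infer that the 80% is sound per test and only needs a label.** It is not sound for 0.2 SD if 199 is the two-arm total.

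The core survives all four. The power is stated at an unadjusted 0.05, the results are to be FDR-adjusted, and nothing connects them. For a design with exactly 80% per test, power for a lone effect is below 80% in any family of two or more tests (71% with two, from Φ(2.802 − 2.241)), and in the 12-test simulation it stays below 80% even when every outcome is affected. Replacing 199 by 786 would not cure this, because 786 gives 80% only at an unadjusted 0.05.

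**Conclusion.** The point holds as a mismatch between the power statement and the analysis rule; the loss of power is a range, not one figure. If the family has 12 tests and the design has 80% per test, per-outcome power under BH lies between about 48% (one outcome affected) and 74-77% (all affected). For a lone 0.2 SD effect with 800 analysed, it lies between 67% and 40% for 3 to 24 tests. These results assume two-sided tests and, for the simulation, equal correlations of 0 to 0.5 between outcomes. The continuous result needs no prevalence. The categorical result does, and no single shortfall can be claimed for it. The 199 is a separate fault in the same sentence, and the larger one if it is meant as a two-arm total.

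**What to change.** Keep the FDR procedure. In the amendment's SAP:

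1. List the p-values in the primary FDR family, saying whether each ASQ domain, age, ITSEA score, dichotomised version and protocol-based repeat is included.
2. Restate the power under that rule for the expected analysed N. If the family has 12 tests, the lone effect detectable with 80% power is about 0.26 SD with 800 analysed and 0.29 SD with 640. For families of 3 to 24 tests it is 0.23 to 0.28 SD with 800.
3. Give the detectable odds ratio with its prevalence assumption and a range: for 12 tests and 800 analysed, about 2.7 at 5% to 1.8 at 20%.
4. In the same edit, correct or explain 199.
5. Interpret null results against the restated detectable effects, not against 0.2 SD and an odds ratio of 2.0.

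The cost is SAP wording and a short recalculation. No participants or procedures are added. The stated power for the 0.2 SD target becomes less favourable.

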## STATISTICAL ANALYSIS PLAN

### Sample size calculation and statistical analyses

We aim at detecting a 0.2 SD unit difference between continuous bone strength parameters; bone mineral content and cross-sectional area. In order to reach a statistical power of 90% with significance level of 0.05, a total of 210 and 297 measurements, respectively, are necessary. In addition, challenges in measuring infants with pQCT may occur. According to previous studies, small children suffer from an average of 6 infections annually. In order to detect a decrease from 12 to 9 infections during the 24-month study period, a sample size of 220 in each group is required. We estimate a possible drop-out rate of 20%. Taking into consideration all the aforementioned aspects, the trial is designed for 1000 subjects: 500 subjects in each intervention group.

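### The 199 participants stated for a 0.2 SD difference do not fit the two-arm comparison, which needs 394 per group (788 in total)

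*Combined protocol and SAP*

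**What the plan says.** The neurodevelopment amendment makes ASQ scores at 12 and 24 months and ITSEA scores at 24 months its primary outcomes. Its section on sample size sets the target for the continuous scores: "We aim at detecting a 0.2 SD unit difference between continuous variables". It also names odds ratios above 2.0 for the categorical outcomes. It then gives the requirement: "In order to reach statistical power of 80% with significance level of 0.05, a total of 199 and 572 participants, respectively, are necessary". The first number belongs to the continuous outcomes and the second to the categorical ones. The planned sample is 1000. On losses it adds: "We estimate a possible drop-out rate of 20% for each follow-up".

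The amendment names neither the test nor the sidedness behind these numbers. The design comes from the main documents: two randomised dose groups (Protocol, Participants and methods), 500 in each (main SAP, sample size section). The main SAP gives a single 20% drop-out figure for the trial.

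**The concern.** A difference of 0.2 SD between two independent groups is small, and a total of 199 is too few to detect it with 80% power. The number is what one would expect for a single sample or for paired differences, and this trial has neither.

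A reader who trusts the 199 will set it against 1000 randomised, or 800 after 20% loss, and see a margin of 1000/199 = 5.0 or 800/199 = 4.0. With such a margin, a null ASQ or ITSEA result would look like strong evidence against an effect of 0.2 SD. If the margin is not there, that reading is too strong.

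**Working it through.** **Inputs.** Difference 0.2 SD, power 80%, significance level 0.05, stated total 199, planned sample 1000, and 20% drop-out per follow-up (neurodevelopment amendment, sample size section). Two groups, 1:1 (main Protocol and main SAP). Two-sided testing is assumed, because sidedness is not stated. Below, δ = 0.2, and z(0.975) + z(0.80) = 1.960 + 0.842 = 2.802.

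**1. Reproducing 199.** For one sample or paired differences, n = 2.802²/δ² = 7.849/0.04 = 196.2 by the normal approximation. The t-test gives 198.15, rounded up to 199, which is an exact match. A linear regression with one predictor and f² = 0.04 also gives 199.

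**2. The two-arm requirement.** n per group = 2 × 7.849/0.04 = 392.4, so 393 per group (786 in total) by the normal approximation. The two-sample t-test gives 393.4, so 394 per group and **788 in total**. Allowing for 20% loss, 788/0.8 = 985 randomised. The stated total is 199/788, about a quarter of the requirement.

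**3. Could another reading rescue 199?**

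- As a number per group (398 in total): power is 51%.
- One-sided test: 310 per group, 620 in total.
- Regression on group: a difference of 0.2 SD between two equal groups has f² = δ²/4 = 0.01, not 0.04, and needs 787 in total.

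None gives 199 for the randomised comparison.

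**4. Power and detectable difference.** For total N in two equal groups, power ≈ Φ(δ√N/2 − 1.960), and the difference detectable with 80% power ≈ 2.802 × 2/√N. The table gives the two-sample t-test values.

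| Total analysed | Where it comes from | Power for 0.2 SD | Detectable at 80% power |
|---|---|---|---|
| 199 | stated requirement | 28.9% | 0.40 SD |
| 640 | 1000 × 0.8 × 0.8 | 71.4% | 0.222 SD |
| 800 | 1000 × 0.8 | 80.6% | 0.198 SD |
| 1000 | no loss | 88.5% | not calculated |

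As a hand check at N = 199: 0.1 × √199 − 1.960 = −0.549, and Φ(−0.549) = 0.291.

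**5. The real margin.** 1000/985 = 1.015. Power of 80% holds up to a total loss of 1 − 788/1000 = 21.2%, and the plan expects 20%.

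**The case against.** The strongest reply is that 199 decided nothing. The main SAP had already set the sample at 1000, and 985 fits within it. Estimates, tests and error control do not depend on the number. The amendment also describes its false discovery rate procedure in the past tense, and the later amendment on psychiatric symptoms refers to a previous study, so the analysis may well be complete. All of this stands. It bears on how to correct the number (a dated note rather than overwriting) and shows that enrolment need not change. It does not make 199 right.

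A second reply is that the source of 199 is unknown. That also stands: the one-sample test is an inference, since the regression route gives the same number. Neither route fits a 0.2 SD difference between two groups.

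Three stronger readings are tempting, and the documents do not support them.

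- *Power at 24 months is below 80%.* This requires the 20% to compound over the 12- and 24-month follow-ups. The wording can equally mean that 20% of those randomised are missing at each assessment, which agrees with the single 20% in the main SAP and leaves 800 and 80.6%. At 12 months 800 remain on either reading. Even with 640, covariates explaining about 19% of the outcome variance (1 − 640/788) would restore about 80% power, though the plan names none.
- *A definite figure for power after false discovery rate adjustment.* Adjusted p-values are never smaller than unadjusted ones, so power for a single outcome cannot rise. How far it falls depends on the number of tests and their correlation. The documents give neither and do not list the tests in each family.
- *The 572 is wrong too.* No event rate is stated. For an odds ratio of 2.0, two-proportion totals without continuity correction run from 1032 at an assumed 5% in the lower-rate group, through 566 at 10%, to 344 at 20%. So 572 is consistent with a two-arm calculation. The rate is a missing detail that only the authors can supply.

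**Conclusion.** The point holds for the continuous outcomes. A total of 199 does not give 80% power for 0.2 SD between two randomised groups. It gives about 29%, and the requirement is 788, about four times the stated number. The plan is adequate or slightly short rather than amply powered: 80.6% with 800 analysed, 71.4% with 640. The documents do not settle which applies at 24 months, so a shortfall there is possible but not shown.

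These figures assume a two-sided test at 0.05, equal groups, no covariate adjustment and no multiplicity adjustment. That 199 is wrong does not depend on the two-sided assumption, since a one-sided test still needs 620.

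**What to change.** In the sample size section of the neurodevelopment amendment:

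- Correct 199 to 788 (394 per group), naming the two-sample test and its sidedness. If the analysis is complete, do this by a dated correction note that leaves the superseded number visible.
- State whether the 20% is a share of those randomised at each follow-up or compounds from one follow-up to the next.
- Give the matching power for 0.2 SD from the planned 1000, marked as before false discovery rate adjustment: 80.6% with 800 analysed, or 71.4% at 24 months with 640 analysed (detectable 0.22 SD).

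Enrolment, data collection and analysis do not change. The cost is a few sentences and a less favourable stated margin.

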### Statistical methods

Standard statistical methods such as linear, logistic and Tobit and moderation analytic strategies with R/SPSS/MPlus will be used to study the impact of vitamin D supplementation and/or 25(OH)D concentrations, and relevant covariates, on main outcomes.

If needed, logarithmic transformation for nonnormal variables is performed in order to achieve normal distribution. Main outcome measures are analysed according to intention-to-treat and protocol-based manner.

To account for multiple testing and control for the false detection rate (FDR), *p*-values from the analysis within primary/secondary analysis were used to derive an FDR-adjusted *p*-values with FDR-procedure setting the false discovery rate at 0.05.

## AMENDMENTS TO THE STUDY PROTOCOL AND STATISTICAL ANALYSIS PLAN FROM THE CURRENT STUDY

### PROTOCOL

#### Background

Previous studies have linked lower childhood 25(OH)D levels to increased depressive symptoms, as well as to increased internalizing, and externalizing problems, in later childhood. Psychiatric problems may not be manifest during early childhood but become evident with age as environmental demands increase. Against this background, the aim of this follow-up study was to build upon our previous study and assess the impact of higher dose vitamin D3 supplementation on psychiatric symptoms at ages 6-8 years, an age period characterized by increased demands for self-regulation in concurrence with a still developing prefrontal cortex.

Lower maternal 25(OH)D levels during pregnancy have also been linked to unfavorable offspring mental health outcomes, e.g., increased negative affectivity in infancy, and depression. Our secondary aim was to assess whether a higher-than-normal vitamin D3 supplementation during infancy might mitigate the potential negative impact of lower pregnancy 25(OH)D levels.

#### Primary outcomes

Primary outcomes of the study are childhood psychiatric symptoms at ages 6-8 years, assessed using the parent-reported Child Behavior Checklist (CBCL).

#### Follow-up

Parents completed the 113 question CBCL questionnaire at child ages 6-8 years.

#### Specific methods

#### Psychiatric symptoms

Psychiatric symptoms were assessed using the parent reported CBCL questionnaire. Results from the questionnaire are used to calculate scores for internalizing, and externalizing symptoms as well as total problems. Using ASEBA software, scores are converted to sex- and age-specific T-scores and dichotomized at 64 or above – scores above the cutoff point are considered to reflect clinically significant problems.

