### STATISTICAL ANALYSIS PLAN

#### Statistical methods

Standard statistical methods such as linear and logistic regression with SPSS software will be used to study the impact of vitamin D supplementation and/or maternal 25(OH)D concentrations, and relevant covariates, on main outcomes.

If needed, logarithmic transformation will be used to normalize skewed variables. Outcome measures will be analyzed according to the intention-to-treat principle.

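### The CBCL amendment names neither a primary form (continuous T-score or 64-and-above) nor a primary scale, so any of six results, including the less powerful binary ones, can carry the primary conclusion

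*Combined protocol and SAP*

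**What the plan says.** The point concerns the last amendment in the combined document, which adds the follow-up at 6-8 years (the CBCL amendment).

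- **Primary outcomes:** "Primary outcomes of the study are childhood psychiatric symptoms at ages 6-8 years", measured by the parent-reported CBCL. No variable, scale or form is named.
- **Psychiatric symptoms:** the questionnaire yields "scores for internalizing, and externalizing symptoms as well as total problems". These "scores are converted to sex- and age-specific T-scores and dichotomized at 64 or above", and the outcome definition ends there.
- **Statistical methods:** "Standard statistical methods such as linear and logistic regression with SPSS software will be used" for the main outcomes, with log transformation of skewed variables if needed and analysis by intention to treat. The two models are not ranked, and neither are the three scales.

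The CBCL amendment has no sample-size section, effect size, expected prevalence or multiplicity rule. The neurodevelopment amendment before it, which covers the ASQ and ITSEA questionnaires, has targets: "We aim at detecting a 0.2 SD unit difference between continuous variables" and "Odds Ratios >2.0 in categorical variables". It also has a false-discovery-rate rule. Nothing in the CBCL amendment carries either forward.

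**The concern.** Three scales in two forms give six candidate primary results, and the plan does not choose among them. Two things are at stake.

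The first is selection. A 64-and-above result on one scale could become the headline when the continuous scores show nothing, or the reverse, and either would comply with the plan as written.

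The second is efficiency. If the binary form leads, the comparison uses only whether a child crosses a cut high in the distribution. A modest shift in symptoms across the whole cohort would then usually be missed, although the continuous score from the same questionnaires would have a fair chance of detecting it.

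**Working it through.** **The plan's own figures.** The CBCL amendment has none to reproduce. The nearest are in the neurodevelopment amendment: totals of 199 (0.2 SD) and 572 (odds ratio 2.0) for 80% power at 0.05. For two groups and 0.2 SD, n per arm = 2 × ((1.960 + 0.842)/0.2)² = 393, or 786 in total, so 199 does not reproduce. It matches a one-sample or paired formula. The 572 is nearly reproduced (566) if the control rate is 10%, which is not stated. Neither figure can stand in for a CBCL power statement.

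**Inputs**
- Children per arm: 500 planned (original SAP), less the 20% per follow-up in the neurodevelopment amendment, applied once, twice or three times: 500 × 0.8 = 400; × 0.8 = 320; × 0.8 = 256.
- Shift: 0.2 SD, borrowed from the neurodevelopment amendment.
- T-score distribution: normal, mean 50, SD 10. This is an assumption; the documents give none.
- Test: two-sided 0.05 (sidedness assumed).
- Cut: 64, or 63.5 as a continuity correction for integer scores.

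**Continuous score.** Power = Φ(0.2 × √(n/2) − 1.960).
- n = 400: Φ(2.828 − 1.960) = 80.7%
- n = 320: Φ(2.530 − 1.960) = 71.6%
- n = 256: Φ(2.263 − 1.960) = 61.9%

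The noncentral t gives 80.6%, 71.4% and 61.7%.

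**Dichotomised score.** Power = Φ((|p1 − p0| − 1.960 × √(2p̄(1 − p̄)/n)) / √((p0(1 − p0) + p1(1 − p1))/n)).

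Reference proportion: 1 − Φ(1.40) = 8.1% with the cut at 64, or 1 − Φ(1.35) = 8.9% at 63.5. A 0.2 SD fall gives 5.5% or 6.1%; a rise gives 11.5% or 12.5%.

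Worked case (cut 63.5, fall, n = 400): (0.0279 − 1.960 × 0.01857)/0.01855 = −0.46, so power is 32%.

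| Per arm | Continuous | Cut 64, fall / rise | Cut 63.5, fall / rise |
|---|---|---|---|
| 400 | 81% | 31% / 37% | 32% / 39% |
| 320 | 71% | 26% / 31% | 27% / 32% |
| 256 | 62% | 21% / 26% | 22% / 27% |

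For 80% power at this shift the binary form needs about 1,120 (rise, cut 63.5) to 1,470 (fall, cut 64) per arm, against 393 for the continuous score.

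**Sensitivity to the distribution.** With a sample mean of 45 to 52 and SD of 9 to 10, binary power at 400 per arm runs from about 13% to 45%. Continuous power stays at 81%, because the shift is in SD units.

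**The categorical target.** At this cut a 0.2 SD shift is an odds ratio of only about 1.5 (0.115/0.885 ÷ 0.081/0.919 = 1.48 for the rise; 0.081/0.919 ÷ 0.055/0.945 = 1.51 for the fall, inverted). Taking the neurodevelopment amendment's odds ratio of 2.0 instead, at 400 per arm:
- Doubling of the odds (8.1% to 14.9%, or 8.9% to 16.3%): binary power 86% to 89%. As a location shift this is about 0.36 SD, where the continuous score has over 99%.
- Halving (8.1% to 4.2%, or 8.9% to 4.6%): binary power about 63% to 66%. As a location shift this is about 0.33 SD, where the continuous score again has over 99%.

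At 256 per arm the halving gives about 45% to 48% binary and about 96% continuous.

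**The case against.** **The figures are conditional.** This stands. The CBCL amendment states no effect size, number or distribution. A reader might infer that the planned analysis has about 32% power. The documents do not support that: the figure is one cell of a table built on a borrowed shift, an assumed distribution and a single 20% loss.

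**The programme's categorical target is larger than 0.2 SD.** This also stands. The neurodevelopment amendment's examples for an odds ratio above 2.0 include possible clinically significant problems, the closest analogue to a T-score of 64 or more. At that target the binary form is adequately powered at 400 per arm for a doubling, so it is wrong to call it underpowered whatever the effect. But the CBCL amendment's Background links lower vitamin D to more symptoms, so the hoped-for effect is a reduction, and for a halving power falls short of 80%.

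**A continuous analysis is already planned.** Linear regression is named, and log transformation is allowed. A reader might infer from the outcome definition that the continuous score is thrown away; it is not. Naming both models without ranking them is what leaves the choice open.

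**The clinical-range proportion is a legitimate estimand.** It is, and an effect confined to the upper tail could favour it. That supports reporting it, not leaving precedence unstated.

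**The continuous form may itself fall short.** At 0.2 SD it has 62% power at 256 per arm. Naming it primary improves the position but does not guarantee 80%.

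**The cut-off wording.** After the 64-or-above rule, the text adds that "scores above the cutoff point are considered to reflect clinically significant problems". Read literally, this excludes a score of exactly 64, but the operative rule is explicit and the slip is clerical.

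**Conclusion.** The point holds as one about an unranked primary outcome. The CBCL amendment leaves six results able to carry the primary conclusion, three of them in a form that is much less efficient for a general shift in symptoms. With a 0.2 SD shift, normal T-scores (mean 50, SD 10) and two-sided 0.05, dichotomising takes power from about 81% to 31-39% at 400 per arm, from 71% to 26-32% at 320, and from 62% to 21-27% at 256. The exact sizes depend on those assumptions. The ordering held in every scenario tried, including odds ratios of 2.0 and 0.5, provided the effect is a location shift.

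A reader might also infer that a result was, or will be, picked after the fact. The documents show only that the plan does not prevent it.

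**What to change.** Add to the CBCL amendment's Statistical methods:
- The primary analysis is the linear comparison of the continuous T-score between randomised groups.
- The three scales are tested in a fixed order, for example total problems, then internalizing, then externalizing. Each is tested at two-sided 0.05, and testing continues only while the preceding scale is significant.
- The logistic analysis of T-scores of 64 or above is supportive, is reported for all three scales with odds ratios and confidence intervals, and cannot by itself carry the conclusion.

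State when the order was fixed and whether results by group had been seen, since the Follow-up section already describes questionnaire completion in the past tense. Use the 64-or-above wording throughout.

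The cost is SAP wording only, with no new data. The headline becomes a mean difference rather than a clinical-range odds ratio, which is still reported. If the first scale is not significant, the other two become descriptive. The choice of total problems first is an example; the documents do not settle it, and the investigators should.
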